## Abstract

**Background:**

Vitiligo is a chronic skin disorder presenting with depigmentation, the pathogenesis of which is complex but the autoimmune theory is now preferred. Multiple immunologic processes, including stimulation of the T-helper (Th)1 response, formation of autoreactive melanocyte-specific CD8^+^ T lymphocytes, a decrease in the blood concentration of T regulatory (Treg) cells, and an increase in interleukin (IL)-17 and interferon (IFN) concentration, have been shown to contribute to vitiligo progression and maintenance. The aim of this study is to evaluate the influence of simvastatin and atorvastatin on vitiligous lesions in patients with nonsegmental vitiligo (NSV). According to available data, statins act through several immunological pathways, potentially reversing undesirable phenomena underlying autoimmune vitiligo pathogenesis.

**Methods/design:**

A study has been designed as a single-center, randomized, double-blind, placebo-controlled pilot study with the enrollment of at least 24 active NSV patients presenting with vitiligous lesions on both upper and lower limbs. The clinical effects of ointments containing 1% simvastatin-acid sodium salt or 1% atorvastatin calcium salt applied on a preselected limb will be assessed in comparison with vehicle ointment applied on the opposite limb. All study participants will undergo clinical evaluation using body surface area (BSA) and Vitiligo Area Scoring Index (VASI) scales at baseline and at weeks 4, 8, and 12 time points. A precise assessment of skin lesions will be performed using photographic documentation obtained during each study visit and processed with NIS-Elements software.

**Discussion:**

Currently available vitiligo topical therapeutic approaches including calcineurin inhibitors and corticosteroids remain poorly effective and are associated with either relatively high cost or potentially dangerous adverse effects. The clinical application of orally administrated statins, widely used as systemic cholesterol-lowering agents, in vitiligous patients has only been tested in two clinical trials; however, data on their potential usefulness is scarce. Moreover, due to a high risk of clinically significant toxicity, topical administration was recommended by researchers. This study is the first to evaluate safety and efficacy of the topical use of statins in patients presenting with NSV.

**Trial registration:**

Clinicaltrials.gov, NCT03247400. Registered on 05 August 2017.

**Electronic supplementary material:**

The online version of this article (10.1186/s13063-018-3168-4) contains supplementary material, which is available to authorized users.

## Background

Vitiligo is a chronic dermatosis with an incidence in the general population ranging from 0.5 to 1.0%. It is associated with the occurrence of depigmented skin lesions that appear due to melanocyte destruction. The etiology of vitiligo comprises genetic and autoimmune predispositions, as well as biochemical, neurochemical, and environmental factors. Until now, the autoimmune hypothesis of vitiligo etiology seems to be the most preferred [1, 2]. Skin and blood of patients with an active form of vitiligo is abundant with autoreactive, melanocyte-specific CD8^+^ T lymphocytes, which are considered to be critical and sufficient for the initiation of depigmentation [3, 4]. Active CD8^+^ T lymphocytes produce interferon (IFN)-γ which, accompanied by tumor necrosis factor (TNF)-α, represents the cytokine profile characteristic of a T-helper (Th)1 cell response. The stimulation of a Th1 response plays a pivotal role in the pathogenesis of vitiligo. It has been shown that the chemokine IFN-γ axis in murine models with focused vitiligo is crucial for both progression and maintenance of vitiligous lesions [5–7]. Statins, acting directly on melanocyte-specific CD8^+^ T lymphocytes, lead to their limited proliferation as well as to decreased IFN-γ production in murine vitiligo models [7, 8].

Additionally, the pathogenesis of vitiligo is associated with a decreased skin concentration of interleukin (IL)-10, which belongs to the family of Th2-dependent cytokines [9, 10]. As a result of the actions of statins, a noticeable increase in anti-inflammatory cytokine (IL-4, IL-5, and IL-10) secretion can be observed. Moreover, a shift to a Th2-dependent response occurs [11, 12].

IL-17, a cytokine that stimulates production of TNF-α, has been reported to be present in higher concentrations in the serum and tissue in vitiligous patients. Vitiligo maintenance has also been proven to be associated with an increased IL-17 concentration [13]. Another cell population that plays an important role in pathogenesis of vitiligo is T regulatory lymphocytes (Treg). It has been found that a decreased peripheral blood concentration of Tregs, as well as their impaired activity, are responsible for an enhanced destruction of melanocytes. As a result of statin use, inhibition of T cell differentiation into Th-17 cells secreting IL-17 can be observed. Furthermore, the process of differentiation into the Treg subpopulation potentiates. These phenomena result in inhibition of inflammatory processes and lead to immunotolerance [14, 15]. Statins have also been found to cause lymphocyte anergy. According to the available data, the impairment of lymphocyte migration as well as a reduced influx to the inflammatory site underlie this condition [16, 17]. On the basis of all the presented pathogenetic mechanisms of acquired vitiligo, we hypothesized that the use of statins may be beneficial for the development of vitiligous lesions and the appearance of repigmentation. Thus, we designed a study aiming to evaluate the influence of topical statin use on repigmentation in patients suffering from nonsegmental vitiligo (NSV).

## Methods

### Design

The study has been designed as a single-center, randomized, double-blind, placebo-controlled pilot trial. The study period has been set between October and March to eliminate any potential positive influence of sunlight on vitiligous lesion repigmentation. Recruitment started on 1 December 2016. The study end date is anticipated to be 30 April 2019. The study population will comprise patients with the NSV acrofacial active form of vitiligo. Upper and lower limb involvement is an obligatory inclusion criterion in screened patients. A total number of at least 24 enrolled patients is planned for the study. All enrolled participants will apply ointment including 1% simvastatin-acid sodium salt onto a preselected limb and vehicle ointment onto an opposite limb and 1% atorvastatin calcium salt ointment onto another preselected limb and vehicle ointment onto an opposite limb, taking into account different combinations as presented in Fig. 1. Such a scheme of ointment administration allows a direct comparison of the effects of active substance and placebo due to the identical biological model and a similar area of vitiligous lesions.

**Fig. 1 Fig1:**
[figure not shown]
Ointment application scheme in the EVRAAS study

The simvastatin-acid sodium salt was obtained from the Department of Organic Chemistry, Nicolaus Copernicus University, Collegium Medicum in Bydgoszcz, according to a previous publication with modifications [18]. The initial studies performed in The Department of Pharmaceutical Technology, Nicolaus Copernicus University, Collegium Medicum in Bydgoszcz, revealed that 1% simvastatin-acid sodium salt and 1% atorvastatin calcium salt can permeate through stratum corneum and reach the stratum basale of the epidermis. The evaluation of the permeability of active substances through the skin was performed in diffusive chambers, taking into account their lipophilic structure and appropriately low molecular weight. Ointments with active substances as well as vehicle ointments will be prepared using an absorption base with the addition of a sorption promotor in The Department of Pharmaceutical Technology. Ointments will be prepared using an Unguator mixing device and they will be placed in polypropylene/polyethylene sterile containers to achieve at least 30-day chemical stability and sunlight protection. After production, study substances will be delivered to the Clinic of Dermatology, Sexually Transmitted Diseases and Immunodermatology, Nicolaus Copernicus University, Collegium Medicum in Bydgoszcz. During the screening visit all patients will undergo blood sample collection to assess the following parameters: peripheral blood morphology, creatine kinase (CK), aspartate aminotransferase (AST), alanine aminotransferase (ALT), creatinine, estimated glomerular filtration rate (eGFR), blood urea nitrogen (BUN), C-reactive protein (CRP), lipid profile, serum glucose, parathormone, cortisol, thyroid stimulating hormone (TSH), free triiodothyronine (fT3), free thyroxine (fT4), antithyroglobulin antibodies, antithyroid peroxidase antibodies, anti-Treponema pallidum antibodies, and antinuclear antibodies (ANA-HEp-2). The laboratory test assessment aims to evaluate each patient’s current metabolic status as well as potential coexistence of autoimmune disease or infection. After the screening visit, four visits will be scheduled for all enrolled participants (baseline at week 0, week 4, week 8, and week 12). Each visit will include the evaluation of vitiligo severity using the numerical scales body surface area (BSA) and Vitiligo Area Scoring Index (VASI). Photographic records of vitiligous lesions obtained during each visit will be processed using NIS-Elements software for detailed lesional skin area measurements. All visits will be held in the same clinical study room, and photos will be taken with a Nikon D5500 camera under similar conditions. At each visit, the participants will be provided with a set of containers including study drugs. The weight of each container will be recorded at the moment of dispensing and after a 30-day period of ointment application.

The patient flow chart throughout the study and EVRAAS study schedule are presented in Figs. 2 and 3, and the complete SPIRIT checklist is provided in Additional file 1.

**Fig. 2 Fig2:**
[figure not shown]
Patient flow chart through the EVRAAS study. BSA body surface area, VASI Vitiligo Area Scoring Index

**Fig. 3 Fig3:**
[figure not shown]
SPIRIT checklist showing the EVRAAS study checklist. BSA body surface area, VASI Vitiligo Area Scoring Index, W week

### Objectives

#### Participants

All study procedures will be conducted with full respect for the regulations included in The Declaration of Helsinki as well as in Good Clinical Practice Guidelines.

According to the study protocol, adult patients of the Clinic of Dermatology, Sexually Transmitted Diseases and Immunodermatology, Nicolaus Copernicus University, Faculty of Medicine in Bydgoszcz, diagnosed with active form of acquired nonsegmental acrofacial vitiligo will be screened for eligibility. Any study-related procedures will be undertaken only after obtaining informed consent from each participant. The main inclusion criteria include male or nonpregnant female (based on female patient declaration) patients aged 18–80 years with a clinical diagnosis of active NSV acrofacial vitiligo with obligatory upper and lower limb involvement and provision of an informed consent form. An active form of vitiligo is defined as the appearance of new areas of depigmentation or progression of existing areas of depigmentation within 3 months preceding screening. Major exclusion criteria include pregnancy or breast-feeding, diagnosis of segmental, mixed, or undefined vitiligo, hypersensitivity to simvastatin or atorvastatin, the use of any systemic statin, azathioprine, methotrexate, mycophenolate mofetil, Janus kinase (JAK) inhibitors, or any investigational drug within 8 weeks preceding screening, and the use of cyclosporine A, systemic corticosteroids, phototherapy, or any other topical or systemic vitiligo treatment within 4 weeks preceding screening. The complete list of inclusion and exclusion criteria is presented in Table 1.

**Table 1 Tab1:** A complete list of inclusion and exclusion criteria for the EVRAAS study

Inclusion criteria^a^	Exclusion criteria^b^
1. Patients of the Clinic of Dermatology, Sexually Transmitted Diseases and Immunodermatology, Nicolaus Copernicus University, Faculty of Medicine in Bydgoszcz 2. Provision of an informed consent form prior to any study procedures 3. Diagnosis of NSV acrofacial vitiligo with upper and lower limbs involvement 4. Active vitiligo, defined as appearance of new areas of depigmentation or progression of existing areas of depigmentation within 3 months preceding screening 5. Male or nonpregnant female patients aged 18 to 80 years 6. Confirmed valid health insurance	1. Pregnancy or breastfeeding 2. Diagnosis of segmental, mixed, unclassified, or undefined vitiligo 3. Hypersensitivity to simvastatin or atorvastatin 4. Any statin use within 8 weeks preceding eligibility screening 5. Systemic immunosuppressive/immunomodulating treatment (i.e., cyclosporine A, corticosteroids) within 4 weeks preceding eligibility screening or azathioprine, methotrexate, mycophenolate mofetil, or Janus kinase (JAK) inhibitors within 8 weeks preceding eligibility screening 6. Phototherapy due to vitiligo or any other medical conditions within the 4-week period preceding eligibility screening 7. Any topical or systemic additional vitiligo treatment (e.g., antioxidants, *Ginkgo biloba*, dermocosmetics) within 4 weeks preceding screening 8. Surgical treatment of vitiligous lesions within the past 4 weeks 9. Decompensated autoimmune or internal diseases 10. Alcohol or drug abuse 11. Skin malignancies (current or a history of skin malignancy within 5 years preceding screening) 12. Presence of skin characteristics that may interfere with study assessments 13. Patients currently participating in any other clinical study 14. Uncooperative patients

*NSV* nonsegmental vitiligo

^a^All inclusion criteria must be met

^b^No exclusion criteria can be met

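### Pregnancy is an absolute exclusion, but entry relies on the patient's own declaration and the itemised screening blood panel contains no pregnancy test

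*Protocol article*

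**What the plan says.** Non-pregnancy is required twice. The Participants section admits, besides men, a "nonpregnant female (based on female patient declaration") aged 18 to 80, and inclusion criterion 5 in Table 1 repeats the requirement for the same age range without naming a method. On the exclusion side, the same section says "Major exclusion criteria include pregnancy or breast-feeding", Table 1 lists it first as "1. Pregnancy or breastfeeding", and the table's footnote adds "No exclusion criteria can be met".

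The only method given for establishing non-pregnancy is the patient's declaration.

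The Design section, in the text after Figure 1, describes the screening laboratory work: "During the screening visit all patients will undergo blood sample collection to assess the following parameters". The list is itemised and ends with "anti-Treponema pallidum antibodies, and antinuclear antibodies (ANA-HEp-2"). The stated aim of the panel is to assess each patient's "current metabolic status as well as potential coexistence of autoimmune disease or infection".

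According to the Intervention section, every enrolled patient receives both statin ointments and two vehicle ointments, one per limb, for twice-daily use over 12 weeks.

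**The concern.** A declaration can report only what the patient knows. It works for a recognised pregnancy and fails for an unrecognised one, which is the case where the criterion depends most on the method of checking. A patient can answer honestly, the site can follow the plan exactly, and a woman who meets the first listed exclusion is still enrolled.

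Participant safety is at stake, together with the trial's ability to enforce its own eligibility rule. In a parallel-group trial some wrongly enrolled patients would be allocated to vehicle alone. Here nobody is: anyone enrolled is assigned both active ointments.

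This is not detail left to a longer document. The article itself names the method, so the question is whether the named method fits the criterion.

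**Working it through.** No arithmetic is needed, and the plan gives no figure on this point to reproduce. The check sets the relevant parts of the protocol article side by side.

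1. **How strict is the criterion?** Pregnancy is exclusion 1 in Table 1, non-pregnancy is part of inclusion 5, and the footnotes require all inclusions to be met and no exclusion to be met. The article leaves no room for discretion.

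2. **Who can be affected?** Both sexes are eligible, aged 18 to 80, so women of childbearing potential are within the target population. Their expected share of the planned sample of at least 24 is not given.

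3. **How is the criterion checked?** By declaration, in the parenthesis of the Participants section. Table 1 gives no method, so it neither adds a check nor contradicts the text.

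4. **Does the screening blood work cover it in another way?** The panel consists of blood morphology, CK, AST, ALT, creatinine, eGFR, BUN, CRP, lipid profile, glucose, parathormone, cortisol, TSH, fT3, fT4, two antithyroid antibodies, anti-Treponema antibodies and antinuclear antibodies. That makes 19 items, none of them a pregnancy test. The panel's stated purposes are metabolic status, autoimmune disease and infection, so pregnancy is not among its aims either.

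5. **What follows for an unrecognised pregnancy?** The patient declares that she is not pregnant. Nothing in steps 3 and 4 contradicts her, and she is enrolled while meeting exclusion 1.

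6. **What is she then exposed to?** Both statin ointments, since every enrolled patient receives both. The treatment period is 12 weeks. This is the longest the exposure could last, because the pregnancy may be recognised sooner.

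7. **Can the harm be sized?** That would take three quantities: the rate of unrecognised pregnancy at screening, the systemic absorption of the ointments, and the fetal risk at that level of absorption. The article gives none of them. On absorption it says only that the active substances pass the stratum corneum and reach the basal layer of the epidermis.

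**The case against.** The strongest reply is that nothing here is contradictory. A trial may exclude pregnancy and establish it by declaration, and a wish for a stronger method is only a preference. The treatment is topical, the Discussion reports no serious adverse events with topical statins in other conditions, and the point has no bearing on the primary outcome, randomisation, blinding or analysis.

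Part of this stands. There is no internal contradiction, and the statistical validity of the trial is not in question. But the article excludes pregnancy without exception, and its safety remark on topical statins does not address pregnancy. The mismatch between an absolute criterion and a check that cannot see the unrecognised case remains.

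Figures 2 and 3 (the flow chart and the visit schedule) were not available for this check, so a test shown there cannot be ruled out. It would conflict with the wording of the Participants section, and the two would then need to be reconciled.

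A reader might also infer three stronger claims, none of which the article supports:

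- **Loss of data.** One might argue that such a patient would be withdrawn, costing 1/24 = 4.2% of the planned minimum sample and both of her limb pairs. The article states no withdrawal rule for pregnancy; the premature termination it describes is for a need to start systemic statins. Even if she stopped early, observations from weeks 4 and 8 might exist.
- **A measured exposure or fetal harm.** Twice-daily use for 12 weeks gives 12 × 7 × 2 = 168 applications of each statin ointment. That is a ceiling, and it says nothing about how likely or how serious the problem is.
- **Missing checks during treatment.** The text mentions no repeat check at later visits. That is an omission which a condensed article may leave to the full protocol, and it is not a fault in what this article fixes.

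**Conclusion.** The point holds in a limited form. The article fixes a method of ascertainment that cannot detect an unrecognised pregnancy, although pregnancy is an absolute exclusion and a blood sample is taken from every patient at screening. Following the plan as written can therefore enrol a woman who meets exclusion 1 and assign her both statin ointments for up to 12 weeks.

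How often this would happen and how much harm would result cannot be stated from the document. The conclusion needs no such figures. It rests on two readings: that the declaration is the only check, as the Participants section says, and that the itemised panel in the Design section is complete. It is a matter of participant safety and of enforcing the trial's own criterion. The change is worth making because it is small and the trial is described as still recruiting, so it can still protect women not yet enrolled.

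**What to change.** In the Participants section, replace the parenthesis that rests on the patient's declaration with a negative pregnancy test at screening for women of childbearing potential. Name the same method at inclusion criterion 5 in Table 1, and add the test to the screening panel in the Design section for that subgroup, so that the three places agree.

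The test can be run on the blood sample already drawn at screening. The cost is one extra assay for each woman of childbearing potential, with no new visit, staff or procedure. Ointments, randomisation and analysis stay as they are. The change covers pregnancies detectable at screening; it does not address any that begin later.

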#### Intervention

All enrolled patients will receive four containers with the following ointments: 1% simvastatin-acid sodium salt, 1% atorvastatin calcium salt, and two vehicle ointment-filled containers labeled with a preselected limb as follows: “left upper limb”, “right upper limb”, “left lower limb”, and “right lower limb”. In each case, application of an active substance to a particular limb is associated with application of the vehicle ointment onto the opposite limb as previously described. The exact description of the randomization process is presented below.

Study participants will apply ointments twice daily (every 12 h) according to the container labels. An approximate amount of 1 cm of ointment is advised for palm-sized lesions. Study drugs must be stored at room temperature.

During the study period, participants are not allowed to initiate treatment with systemic statins due to any other medical conditions. In case of a necessity to start statin uptake during the study period, the patient’s participation will be prematurely terminated. Moreover, administration of any other topical active substances on lesional areas is forbidden throughout the study period. The systemic use of any immunosuppressive or immunomodulating medications, as well as laser therapy or phototherapy, is not allowed throughout the study.

Participants are not allowed to use any other additional vitiligo treatment, either systemic or topical, including the use of antioxidants, *Ginkgo biloba*, or dermocosmetics.

The study period was defined as 12 weeks. The visit schedule includes a screening visit, when all necessary data including blood sample results will be gathered, baseline (week 0) and three evaluation visits every 4 weeks (week 4, week 8, and week 12). During each visit all participants will be provided with a new set of previously weighed study drugs. Previously distributed containers need to be returned at each visit, and their final weight will be recorded in the study documentation after return. Photographic documentation of vitiligous lesions will be recorded during each visit.

Sunbathing is prohibited throughout the whole study period.

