#### Secondary outcomes

Secondary outcomes of the study comprise safety and tolerability of the study drugs, assessed as the number of participants with treatment-related adverse events according to Common Terminology Criteria for Adverse Events (CTCAE) version 4.0, the percentage of patients who achieved particular response rates (none, 0%; poor, 1–25%; moderate, 26–50%; good, 51–75%; excellent, > 75%) in each arm assessed as a relative reduction in lesional skin area, as well as with the BSA and VASI scale, a comparison of simvastatin and atorvastatin efficacy between study participants, the association between disease duration and repigmentation rate in the study arms, and the association between estimated daily ointment use (grams per square centimeter of skin) and the repigmentation rate in study arms.

The complete list of study outcomes is presented in Table 2.

**Table 2 Tab2:** A complete list of the EVRAAS study outcomes

Primary outcome	Secondary outcomes
1. Evaluation of repigmentation of vitiligous lesions achieved after the administration of 1% simvastatin-acid sodium salt or 1% atorvastatin calcium salt ointments compared with vehicle ointment after a 12-week study period (change from baseline in repigmentation on BSA and VASI scale).	1. Number of participants with treatment-related adverse events as assessed by CTCAE version 4.0 2. Percentage of patients who achieved particular response rate in each arm assessed as a relative reduction in lesional skin area as follows: none, 0%; poor, 1–25%; moderate, 26–50%; good, 51–75%; excellent, > 75% 3. Percentage of patients who achieved particular response rate in each arm assessed as a relative reduction in BSA scale as follows: none, 0%; poor, 1–25%; moderate, 26–50%; good, 51–75%; excellent, > 75% 4. Percentage of patients who achieved particular response rate in each arm assessed as a relative reduction in VASI scale as follows: none, 0%; poor, 1–25%; moderate, 26–50%; good, 51–75%; excellent, > 75% 5. Comparison of simvastatin and atorvastatin efficacy between study participants 6. The association between disease duration and repigmentation rate in study arms 7. The association between estimated daily ointment use (grams per square centimeter of skin) and repigmentation rate in study arms

*BSA* body surface area, *CTCAE* Common Terminology Criteria for Adverse Events, *VASI* Vitiligo Area Scoring Index

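### The hypersensitivity exclusion covers only the two statins, although every patient applies the same ointment base and sorption promotor to all four limbs

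*Protocol article*

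**What the plan says.** Table 1 in the Participants section is titled "A complete list of inclusion and exclusion criteria for the EVRAAS study". Its third exclusion is "Hypersensitivity to simvastatin or atorvastatin", and the Participants text has the same scope: "hypersensitivity to simvastatin or atorvastatin, the use of any systemic statin".

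On composition, the Design section (the paragraph after Fig. 1) says: "Ointments with active substances as well as vehicle ointments will be prepared using an absorption base with the addition of a sorption promotor".

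On exposure, the Intervention section says: "All enrolled patients will receive four containers with the following ointments". It then lists one simvastatin, one atorvastatin and two vehicle containers, each labelled for one limb. It continues: "Study participants will apply ointments twice daily (every 12 h) according to the container labels". The treatment period is 12 weeks.

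**The concern.** A hypersensitivity exclusion should cover what the patient will actually put on the skin. Here it covers the two active substances, each at 1% and each applied to one limb. It leaves out the base and promotor, which go on all four. A vehicle can itself provoke a reaction in someone sensitised to one of its constituents, and this design leaves no limb without it.

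The stake is first the patient's: someone whose sensitivity is already known could be enrolled and exposed on every limb, when a question at screening would have prevented it. The second stake is the data. Repigmentation is read from photographs and planimetry, and inflamed skin could make lesion edges harder to trace. A participant who leaves takes away the pair for both statins at once, because each participant contributes both.

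**Working it through.** The plan gives no figure to reproduce. The check sets the eligibility rules beside the description of the ointments.

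1. **What touches the skin.** By the Design section, all the ointments contain the base and promotor. By the Intervention section, each patient has four containers, one per limb. So 4 of 4 limbs receive the base and promotor, 1 limb receives simvastatin and 1 receives atorvastatin.

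2. **What the criteria screen for.** Table 1 has 6 inclusion and 14 exclusion criteria. Of the 14 exclusions, one concerns hypersensitivity (criterion 3) and it names the two statins. None of the 14 names the base, the promotor or any other excipient.

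3. **Whether another criterion catches the case.** The nearest is criterion 12: "Presence of skin characteristics that may interfere with study assessments". It concerns features present on the skin at screening. A patient with a known contact sensitivity whose skin can be assessed normally does not meet it. Criterion 9 is limited to decompensated disease. The table's footnotes make the lists operative, so on the text as written this patient is eligible.

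4. **Effect on the main contrast.** The planned analysis compares drug with placebo between the right and left sides of the same patient. Let D and V be the changes on the active and vehicle limbs without a reaction, and let r be the effect of a reaction to the shared base. If r is the same on both limbs, (D + r) − (V + r) = D − V, and the difference is unchanged. If r varies between the two limbs for reasons unrelated to allocation, it adds variance but no systematic shift.

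5. **Scale of a possible loss.** The documents give no frequency of sensitivity to the base, so the number k of participants lost is an assumption. With 24 enrolled, the share of pairs lost for each statin is k/24:
   - k = 0: 0%
   - k = 1: 1/24 = 4.2%
   - k = 2: 2/24 = 8.3%

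   These figures only show what one or two such participants would mean at this sample size. They do not estimate risk.

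**The case against.** The strongest reply is that this is an omission and not a contradiction: the ointment description and criterion 3 do not conflict, and a journal article may leave detail to the full protocol. The title of Table 1 claims completeness, but the table is not literally exhaustive. The Participants text excludes use of an investigational drug within 8 weeks before screening, and Table 1 has no such item (criterion 13 covers only current participation in another study). Its silence on excipients is therefore weaker evidence about the full protocol than the title suggests. That caution stands. What remains is that a hypersensitivity rule is stated, in two places, and its scope is narrower than the exposure described in the same article.

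The scenario is also narrow. It needs a known sensitivity to a constituent and a specialist dermatology clinic that enrols the patient anyway. A history question would not find sensitivity that the patient does not know about. Both points are fair and keep the weight modest.

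Four stronger readings are tempting and are not supported:

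- *The patient would react.* No constituent is named and no reaction rate is given, so the text supports only that the patient could react.
- *The efficacy comparison is biased.* A reaction to the shared base falls on both limbs of a pair, so no systematic bias follows.
- *The participant would be lost.* The Intervention section forbids other topical active substances on lesional areas, but it does not say how a reaction is managed. The only early termination it states is for starting a statin. Loss is possible, but the documents do not establish that it is likely.
- *A wider exclusion would clean up the safety outcome.* Table 2 lists "Number of participants with treatment-related adverse events as assessed by CTCAE version 4.0". Every participant receives both statins and vehicle, so this count does not separate reactions to the base from reactions to a statin, whatever criterion 3 says. That is a separate matter, and new or unrecognised reactions to the vehicle would still be counted.

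**Conclusion.** The gap is real and small. As published, the criteria admit a patient with a known sensitivity to a constituent of the base or promotor, and that patient would apply it to all four limbs. The main consequence is an avoidable safety exposure. The secondary ones are possible noise in the lesion assessment and possible loss of a participant from a small pilot, at 4.2% of pairs per statin for each participant lost from 24. The frequency cannot be given from the documents.

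The conclusion rests on two assumptions: that Table 1 and the Participants text reflect the operative criteria, and that the base and promotor are common to all four containers, as the Design section states. If the full protocol already excludes sensitivity to excipients, only the published wording needs correcting.

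**What to change.** Extend criterion 3 in Table 1 to known hypersensitivity to simvastatin, atorvastatin, or any component of the ointment base or sorption promotor. Make the same change in the Participants summary. Check it with one history question at screening, using a list of constituents from the department that prepares the ointments.

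The cost is one phrase in two places and one question, with no new test and no change to the analysis. The downside is the rare exclusion of a candidate. The change removes known sensitivity only; patients with unrecognised sensitivity can still enter.
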